### **Training of HCW**

Before initiation of the study all HCW in the relevant departments in MMH and CHH will receive an in-house training on CRP POCT. The training will include how to use CRP POCT and interpretation supporting the clinical evaluation of the child. The training will be performed by the PI and research team.

### **Eligibility Assessment**

Neonates 0-28 days and children 29 days to 12 years in the two hospitals MMH and CHH will be assessed against the inclusion criteria by a research assistant. The research assistant will be present in the wards 24 hours during the days Monday to Friday.

## **Informed Consent**

Parents or caregivers of children eligible for inclusion will be approached by research assistants and explained about the study orally and in writing if able to read. The information will include the exact nature of the study, implications and constraints as well as risks and benefits of participation. It will be clearly stated in the patient information sheet and verbally explained to the participant that they are free to withdraw from the study at any time for any reason without impacting their future care, and with no obligation to provide the reason for withdrawal. Consent will be approved by signature or fingerprint by one of the parents or legal caregiver as the participating children are not of legal age.

## **Data Management and analysis**

### **Data management**

Data collection and management will be overseen by the PhD student. In addition each hospital will have a supervisor/research coordinator responsible for data collection and management in that hospital. Data will be entered directly into REDCap through secure tablets and transferred to STATA where analysis will be performed. Informed consent forms will be on paper and all data will be kept confidentially.

### **Data collection tools**

The data collection materials will consist of:

- Informed consent (English and Swahili), appendix 2.1, will be asked by the research assistants.
- Description of available drugs, equipment for treatment such as peripheral venous catheters, i.v. fluids. This will be performed two times during the study, at initiation and end of data collection. The data will be collected by a research assistant. The content for available material is shown in appendix 2.2.
- Inclusion and eligibility assessment for neonates and children respectively, appendix 2.3 and 2.4. The risk factors according to the WHO's guidelines for neonatal sepsis and the use of prophylactic antibiotic will be assessed using a picture of the partogram, the delivery book, the antenatal card and the case file. The admitted neonates and children eligible assessment will be done by case files and admittance books.

- After inclusion the caregiver assisted by the research assistant will complete a questionnaire (English and Swahili) on socio-economic background and health seeking behaviour, appendix 2.5.
- CRP will be taken by the clinician responsible for treatment supported by the research assistant responsible for randomisation and data collection. Clinical data and treatment registration will also include the general examination, respiratory count, temperature, and a blood glucose measurement (capillary point-of-care test) and prescriptions. Emphasis will be put on the use of antibiotics during admission and status of child obtained from the hospital files, appendix 2.6.
- At the time of discharge or death a discharge form will be filled, appendix 2.7. The family will be contacted to enquire about the status of the child after discharge at day 7 and 28 primary by phone, but if not available by home visit of the research assistant, appendix 2.8.
- Questionnaire for the health care worker on their education, work experience and acceptability of using CRP will be conducted at the feasibility phase of the study using a semi-structured questionnaire, appendix 2.9.

Appendix 2.1: Informed consent

Appendix 2.11: Informed consent for healthcare personnel

Appendix 2.2: Available material survey

Appendix 2.3: Inclusion and randomization neonates

Appendix 2.4: Inclusion and randomization children

Appendix 2.5: Socioeconomic background and health seeking behavior

Appendix 2.6: Clinical data registry

Appendix 2.7: Discharge form

Appendix 2.8: Follow-up form

Appendix 2.9: Health worker education and acceptability form

## **Data analysis**

Data analysis will include comparing baseline variables between the intervention and control groups using X tests for categorical variables and t-tests for continuous variables, without adjustment. Baseline characteristics such as age, sex, urban/rural residence, number of children, and study site will be compared. Separate analyses will be conducted for all three sub-groups neonates at risk of infection, neonates with signs of infection and children aged 6 months to 12 years.

The primary outcome duration of antibiotic treatment (days), which is a continuous variable, will be compared between the intervention and control groups using a multivariable linear regression model. Neonates at risk of early onset sepsis are recommended for two days of antibiotic treatment by the WHO. Therefore, in this subgroup, an additional non-inferiority analysis will be conducted using a multivariable logistic regression model, comparing CRP POCT with prophylactic two-day antibiotic treatment on the binary outcome of antibiotic prescribed yes/no. All comparisons will be conducted using both unadjusted and adjusted models for sex, age, and clinical status, following an intention-to-treat (ITT) approach. To account for deviations from CRP-based recommendations, a secondary Per-Protocol (PP) analysis will be conducted, excluding participants who did not adhere to their assigned intervention. For neonates at risk of early-onset sepsis, a non-inferiority comparison will be performed per protocol, assessing whether CRP-guided management is not inferior to standard clinical decision-making. Adherence to CRP-based recommendations will be systematically recorded and analyzed to evaluate its impact on treatment decisions. Statistical analyses will be performed after entering data from the final follow-up and data will be stored in a REDCap database for analysis using STATA.

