### **Study endpoints**

The primary study outcome is the duration of antibiotic treatment (number in 24-hour periods between start and end of antibiotic treatment) within 14 days of the admittance of included neonates and children in each study arm (superiority analysis). Antibiotic use during admittance and a composite measure of antibiotic use during admittance and discharge are reported. For every participant, the types and quantity of antibiotics given during the study period will be assessed based on individual drug administration records. To ensure patient safety in case of reduction in antibiotic use a second primary outcome relapse of infection is measured as reinstitution of antibiotics within 72 h after completion of the initial course of antibiotic treatment.

The secondary study outcomes are:

1. Antibiotic use (prescribed daily doses)
2. Choice of antibiotic drug and dose compared to local standard treatment guidelines
3. Number of days admitted in hospital
4. Number of days until resolution of symptoms
5. Development of clinical signs of sepsis
6. Proportion of cases with blood cultures collected before antibiotic treatment
7. Bacterial pathogens and AST in blood cultures
8. Hospital re-admittance within 14 days
9. Mortality at follow up day 7 and 28

Our definition of prescribed and defined daily doses accords with the recommendations of WHO. The route of administration will be incorporated in the daily dose calculations.

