### **Sample size calculation**

For the superiority primary outcome, the sample size calculation is based on an estimated 20% reduction in duration of antibiotic treatment. Assuming the mean duration of antibiotic treatment of 7 days (168 hours) and an SD of 5 days (120 hours), with an  $\alpha$  of 0.05 and a  $\beta$  of 0.1. The trial needs 262 patients in each group (524 patients in total). However, some patients may be discharged before reaching the stopping rules and these patients would not be stopped according to the CRP guidelines. We assume that 20% of patients are going to be discharged before the stopping rule was enacted or lost to follow-up. To ensure enough power for independent analysis for the three study population groups we apply this power calculation for each group. Furthermore, for children 6 months to 12 years further inflation of sample size by 50% is done to ensure exploration of sub-groups with different symptoms of infection (e.g. pneumonia, diarrhoea etc.). To establish non-inferiority of the second primary outcome of relapse of infection, assuming event rate

of 5% of relapse, non-inferiority margin of 6%, one-sided alpha of 2.5%, power of 90% the sample size is 278 per group i.e. total 556 children plus 20% loss to follow-up equaling 646 children.

Hence, the study aims to include 646 neonates at risk of infection, 646 neonates with suspected infection and 969 children aged 6 months to 12 years with infection - an overall total of 2261 children included. Power calculations were performed using sample size calculators provided by Sealed Envelope (21).

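### Non-inferiority is attached, without a margin, to antibiotic prescribing in at-risk neonates, while the relapse test that was powered is not carried into the analysis section

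*Protocol*

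**What the plan says.** Protocol, Study endpoints: the first primary outcome is duration of antibiotic treatment, tested for superiority. To guard safety if antibiotic use falls, a "second primary outcome relapse of infection is measured as reinstitution of antibiotics within 72 h after completion of the initial course".

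Protocol, Sample size calculation: the second calculation is done "To establish non-inferiority of the second primary outcome of relapse of infection". Its inputs are an event rate "of 5% of relapse, non-inferiority margin of 6%, one-sided alpha of 2.5" per cent and 90% power, which gives 278 per group. The resulting target of 646 is used for each neonatal group and raised by half to 969 for the older children.

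Protocol, Data analysis: duration is assigned a linear regression model. Two non-inferiority statements follow, both confined to neonates at risk of early onset sepsis. The first is a logistic regression "comparing CRP POCT with prophylactic two-day antibiotic treatment on the binary outcome of antibiotic prescribed yes/no", with no margin. The second says that "a non-inferiority comparison will be performed per protocol, assessing whether CRP-guided management is not inferior to standard clinical decision-making"; it names no outcome and no margin. Neither relapse nor the 6% margin appears in this section.

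Protocol, Hypothesis: for at-risk neonates, CRP testing is expected to lower the use of prophylactic antibiotics safely.

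**The concern.** The protocol gives non-inferiority to one outcome when it sizes the trial and to a different one when it describes the analysis. Non-inferiority asks whether something worth protecting has been given up. In at-risk neonates, antibiotic prescribing is what the intervention is meant to reduce, so the natural question is superiority. Whatever the result, it does not tell the reader whether withholding antibiotics did harm.

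At stake is the safety half of the trial's claim. The trial is open-label and fewer antibiotics is its goal. If the analysis section does not carry the relapse test, then the effect measure, the analysis set and the decision rule for a primary outcome remain open. A statistical analysis plan that followed the analysis section would carry the misplaced test forward. One that followed the sample size section would contradict the analysis section.

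**Working it through.** 1. **Reproduce the plan's figure.** Inputs from Sample size calculation: relapse 5%, taken as equal in both arms; margin 6%; one-sided alpha 2.5%; power 90%; 1:1 allocation. With unpooled variance on the risk difference scale:

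   n per group = (1.96 + 1.2816)² × 2 × 0.05 × 0.95 / 0.06² = 277.3, rounded up to 278, or 556 in total.

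   This matches the protocol and shows that the margin is an absolute 6 percentage points.

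2. **Can the planned sizes carry the test?** Power = Φ(0.06/SE − 1.96), with SE = √(2 × 0.05 × 0.95 / n).

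   | Population | n per arm | SE | Power |
   |---|---|---|---|
   | Each neonatal group (646), no loss | 323 | 0.0171 | 93.8% |
   | Each neonatal group, 20% lost | about 258 | 0.0192 | 87.9% |
   | Children (969), no loss | 484 | 0.0140 | 99.0% |
   | Children, 20% lost | about 387 | 0.0157 | 96.9% |

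   The 87.9% falls below 90% because 646 allows for only 1 − 556/646 = 13.9% loss. That is a separate matter and does not affect this point.

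3. **What would non-inferiority on prescribing show?** The protocol gives no prescribing rates, so these are assumptions: 90% or 98% prescribed under standard care, 30% to 70% under CRP guidance, 323 per arm. Difference is CRP minus control, with a 95% CI of ±1.96 × √[p₁(1−p₁)/323 + p₂(1−p₂)/323].

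   | Control | CRP | Difference (points) | 95% CI |
   |---|---|---|---|
   | 98% | 30% | −68 | −73.2 to −62.8 |
   | 98% | 70% | −28 | −33.2 to −22.8 |
   | 90% | 30% | −60 | −66.0 to −54.0 |
   | 90% | 70% | −20 | −26.0 to −14.0 |

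   If being prescribed counts as the good outcome, the lower limit must stay above minus the margin. Even in the mildest row the margin would have to exceed 26 points, so CRP guidance fails because it works. If being prescribed counts as the bad outcome, the upper limit is below zero in every row and any margin is met. The test is then weaker than the reduction the protocol hypothesises. Neither direction bears on relapse.

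4. **Does the relapse definition fit at-risk neonates?** Relapse is defined only after an initial course has been completed. Under the intervention, an at-risk infant with a low CRP may never start one, and so cannot meet the definition. A later first course would be an initial course, not a reinstitution. Suppose relapse is 5% among starters in both arms and never-starters are counted as relapse-free:

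   - 98% against 30% starting: 0.98 × 5% = 4.9% against 0.30 × 5% = 1.5%, a difference of −3.4 points.
   - 98% against 70% starting: 4.9% against 0.70 × 5% = 3.5%, a difference of −1.4 points.

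   On these assumed rates, the CRP arm starts 1.4 to 3.4 points ahead of a 6-point margin through the definition alone. Restricting the comparison to starters would avoid this, but at the price of comparing groups that are no longer randomised.

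**The case against.** The strongest reply is that nothing has been replaced. The Data analysis section presents the prescribing analysis as an extra, prompted by the WHO two-day recommendation. The relapse hypothesis, margin, alpha and power are fixed in the sample size section, and the general rules (separate analyses by population, ITT, secondary per-protocol) are in place. A model and an effect measure can be left to a statistical analysis plan, which is not shown here. All of this stands, and silence on the relapse model alone would not be a finding. What remains is that the section is not silent on non-inferiority. It applies it to an outcome for which it is the wrong question, and adds a second statement with no outcome at all.

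Several stronger readings are tempting, and the protocol does not support them.

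- A reader might infer that prescribing carries the only non-inferiority test. The per-protocol sentence is a second one. Its outcome is unstated, so it does not fill the gap, but it cannot be assumed to concern prescribing.
- A reader might infer that the 646 + 969 = 1,615 participants in the other two populations have no non-inferiority objective. The sample size section gives them one; what is absent is its counterpart in the analysis section.
- A reader might infer that an odds ratio is to be judged against 6 points. The protocol ties logistic regression to prescribing and the margin to relapse, and never sets one against the other.
- A reader might infer that the logistic model will break down because nearly all controls are treated. No prescribing rate is given, and treatment decisions rest with the clinicians.

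**Conclusion.** The point holds in this form: non-inferiority is misapplied, without a margin, to antibiotic prescribing in at-risk neonates; the accompanying per-protocol statement lacks both outcome and margin; and the powered relapse test is not carried into the analysis section for any of the three populations (646 + 646 + 969 = 2,261). It rests on reading the margin as absolute, which the reproduced 278 per group supports. The prescribing and starting rates used above are assumptions; the conclusion about prescribing needs only that CRP guidance lowers it, as hypothesised.

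It does not follow that safety cannot be concluded. A confidence interval for the relapse difference can still be set against the 6 points already stated. Mortality, re-admission and development of sepsis signs are secondary outcomes, and a DSMB reviews safety. Those do not replace the relapse test, but they rule out the absolute claim. For at-risk neonates, that comparison is only interpretable once scoring of infants who never start a course is settled.

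**What to change.** Amend the Data analysis section and reconcile it with Study endpoints and Sample size calculation.

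(a) In at-risk neonates, analyse antibiotic prescribed yes/no as a superiority comparison, reported as a risk difference with a 95% CI, and remove the non-inferiority label.

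(b) State that, in each of the three populations, non-inferiority on relapse is concluded if the upper limit of the two-sided 95% CI for the risk difference (CRP minus control) is below 6 percentage points, in both the ITT and per-protocol sets. This matches the one-sided 2.5% already chosen. Make relapse and the 6-point margin the outcome and margin of the per-protocol non-inferiority sentence.

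(c) Reconcile the relapse definition with at-risk neonates who never start antibiotics, so that every randomised infant is scored on the same footing in both arms and the arm with fewer starters is not favoured automatically. The investigators should choose the definition, before outcome data are compared by arm.

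The cost is protocol wording and a little more analysis. Parts (a) and (b) need no more participants. For (c), antibiotic use is recorded daily during admission and asked about by telephone on days 7 and 28. The forms are not shown, so the team should confirm that they capture the start dates the chosen definition needs.

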- c) For children 6 months to 12 years admitted with fever, history of fever or diarrhoea and in the intervention group, CRP will be taken at admittance and again at 18-24 hours. It will be communicated that if both CRP levels are less than 10mg/L it indicates that the disease is not severe, and antibiotics are most likely not needed and hence can be either not started or discontinued. If the second CRP is between 10mg/L and 50mg/L, antibiotics might be needed depending on whether the trend of the CRP is upwards or downwards. Hence, if antibiotics have been initiated the clinician can consider stopping the antibiotics earlier. If any of the CRP's are more than 50mg/L that it is likely that antibiotics are needed and treatment should be continued, figure 3. At all times the health care workers are instructed to take the clinical picture into account together with the value of the test. With obvious symptoms of bacterial infection with affected general condition, antibiotic treatment may be initiated and continued on clinical indication. The training of health care workers will also include knowledge of CRP pharmacodynamics and cases where a low CRP might need to be interpreted cautiously, e.g. a history of fever lasting less than 24 hrs. HCWs will be instructed to use CRP POCT for all patients in the intervention group and use the information to guide diagnosis and treatment choice. We will use an appropriate machine procured through the Ministry of Health, for instance Aidian QuickRead go CRP POCT set-up. Feasibility of using the CRP POCT will be assessed using the framework provided by Bowen et al describing acceptability, demand, implementation, practicality, adaptation, integration, expansion, limited-efficacy testing (4).

[figure not shown]

Aidian CRP POCT.

The training of HCWs will include the following flowcharts, figure 1 to 3

[figure not shown]

Figure 1: CRP intervention flowchart for neonates with risk factors of early onset sepsis (EOS)

[figure not shown]

Figure 2: CRP intervention flowchart for neonates with signs of infection

[figure not shown]

Figure 3: CRP intervention flowchart for children with febrile illness or diarrhea

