### **Study procedures**

Participants are screened for eligibility at the participating hospitals by a research assistant (RA) prior to routine examination by a clinician. Parents /caregivers of eligible children are requested for informed consent, after having received oral and written information regarding the trial. Participants are then randomized to the intervention group (CRP POCT) or control group (usual care) by a responsible RA through the REDCap Randomization Module (23). Case report forms (CRFs) are filled out by RA for all participants at the first consultation and every subsequent day the participant is admitted. Participants assigned to the intervention group are provided with CRP POCT during consultation with their clinician at admittance and after 18-24 hours of treatment. The CRP POCT is carried out as a prick test using capillary blood. Children in the control group do not have the CRP POC test taken. Decision on the treatment of participants is exclusively the responsibility of the clinicians of the included hospitals. To assess adherence, all treatment decisions including deviations from CRP recommendations are recorded in case report forms (CRFs). Reasons for deviation are documented for transparency and allow for subgroup analysis.

During admission RA follow the enrolled children daily and register

- Demographic details including sex, age, co-morbidities
- Obstetric and neonatal background information
- Duration of clinical symptoms prior to consulting
- Presence of specific and general symptoms
- Clinical assessments and results of clinical examination (oxygen saturation, respiratory rate, blood pressure, heart rate, body temperature)
- All diagnostic tests performed or ordered
- Management: antibiotic, antiviral prescription, other (symptomatic) medication prescribed and advised
- Additional advice: preventive measures for themselves and their family members, time-off, home isolation, hygienic measures
- Referral to other hospitals

Furthermore, HCWs in participating hospitals answer a questionnaire on professional education as well as acceptability of CRP POCT testing during the feasibility study.

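### One adjustment set (sex, age, clinical status) serves three different populations, does not name the entry criterion or symptom duration, and leaves clinical status undefined

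*Protocol*

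**What the plan says.** The Data analysis section of the protocol states "Separate analyses will be conducted for all three sub-groups". Antibiotic duration "will be compared between the intervention and control groups using a multivariable linear regression model". On covariates it specifies, for every comparison, an unadjusted analysis and "adjusted models for sex, age, and clinical status". No covariate is specific to one population, and clinical status is not defined.

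Other sections show what is known about each participant at entry:
- **Inclusion criteria:** children enter through a febrile criterion or a diarrhoeal one. At-risk newborns enter through a WHO risk factor.
- **Data collection tools:** the WHO risk factors are read from the delivery and antenatal records as part of the inclusion assessment.
- **Study procedures:** the recorded items include "Duration of clinical symptoms prior to consulting" and "Obstetric and neonatal background information". Forms are completed at the first consultation and on each later day in hospital.
- **Sample size calculation:** the children's group is enlarged by 50% for "exploration of sub-groups with different symptoms of infection (e.g. pneumonia, diarrhoea etc".
- **Intervention:** staff are told to read a low CRP cautiously in some cases, such as "a history of fever lasting less than 24 hrs".
- **Randomisation and blinding:** stratification is by sex and study group only.

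**The concern.** Three points follow from setting these sections side by side.

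1. **The common set fits the populations unevenly.** At-risk newborns are tested at 18-24 hours of life, so age can hardly vary among them. They need no clinical signs to enter, so clinical status may vary little too. What remains is mainly sex, which is already a stratification factor. The risk factor that brought the newborn into the trial is not named.
2. **The protocol treats presentation and symptom duration as informative, but the model does not name them.** Randomisation is not stratified on either, so adjustment is the remaining protection against chance imbalance.
3. **Clinical status has no time point.** With forms filled daily, an analyst could take a value recorded after randomisation. Such a value may be affected by the intervention and should not be adjusted for.

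At stake are some precision on the duration outcome and the reproducibility of the adjusted analysis.

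**Working it through.** **Inputs from the Sample size calculation section**
- Difference: 20% of 7 days = 1.4 days. SD: 5 days.
- Alpha 0.05, taken as two-sided because the section does not say. Power 90%.
- Stated size: 262 per arm.
- Targets: 646, 646 and 969, with 20% early discharge or loss.

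**Reproducing the plan's figure**

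n per arm = 2 × [5 × (1.960 + 1.282) / 1.4]² = 268.05, rounded up to 269. The stated 262 is 7 lower (2.6%) and gives 89.3% power. The one-sided formula gives 219, so two-sided is the reading that fits.

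**Evaluable numbers if the full 20% is removed**
- Each neonatal group: 646 / 2 × 0.8 = 258.4 per arm.
- Children: 969 / 2 × 0.8 = 387.6 per arm.

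**Effect of added covariates**

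If the added terms explain a fraction R² of the variance, the residual SD is 5 × √(1 − R²), and

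power = Φ( 1.4 / [5 × √(1 − R²) × √(2/n)] − 1.960 ).

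For a neonatal group with R² = 0, the standard error is 5 × √(2/258.4) = 0.440, and 1.4 / 0.440 = 3.183. Power is Φ(1.223) = 88.9%.

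| R² (assumed) | Power, neonatal group | Power, children | Equivalent sample, 1/(1 − R²) |
|---|---|---|---|
| 0 | 88.9% | 97.4% | 1.00 |
| 0.02 | 89.5% | 97.6% | 1.02 |
| 0.05 | 90.4% | 97.9% | 1.05 |
| 0.10 | 91.8% | 98.4% | 1.11 |
| 0.20 | 94.5% | 99.2% | 1.25 |

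An R² of about 0.036 brings the neonatal groups to 90% (1 − 258.4/268.05).

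**Interval width in children**

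The 95% half-width is 1.960 × 5 × √(2/387.6) = 0.70 days at R² = 0. At R² = 0.10 it is 0.70 × √0.90 = 0.67 days.

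**Limits of these figures**
- The protocol gives no R² or correlation. The range is illustrative.
- The R² = 0 row credits the existing three covariates with no explained variance.
- The Data analysis section refers to a two-day WHO course for at-risk newborns, so a mean of 7 days with SD 5 may not describe that group. The power figures are least secure there.
- The calculation concerns the linear model for duration. It does not carry over directly to relapse, which is binary.

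**The case against.** **Covariate lists by population usually belong in the SAP, which is not shown.** That is fair for detail the protocol leaves open. Here the protocol names a set and applies it to every comparison, so a different set in the SAP would depart from it. The point stands as an improvement to a stated choice.

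**Clinical status may already cover presentation.** It may: symptoms and examination findings are among the recorded items. Omission of the entry criterion is therefore likely but not certain. This supports defining the term, and it rules out replacing clinical status with other covariates, since it may be as prognostic as any of them.

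**No figure shows that entry criterion or symptom duration predicts antibiotic duration.** Correct. The remark on short fever concerns how to read a CRP value, and the 50% enlargement is for subgroup exploration. Neither establishes prognosis. At R² of 0.02 to 0.05 the gain is only 0.6 to 1.5 points.

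**A reader might infer that the duration outcome is materially underpowered and needs rescue by adjustment.** The documents do not support this. The neonatal figure is 1.1 points below 90% before any credit to the existing covariates, and children are well above 90%. A lower figure of 81.2% appears if all of the 20% are early discharges kept under intention to treat with no effect (0.8 × 1.4 = 1.12 days, 323 per arm). The protocol does not split early discharge from loss, so that is one assumption among several.

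**A reader might also infer that the plan adjusts for a post-randomisation variable.** It does not say so. It only fails to exclude it.

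**Conclusion.** The point holds as a modest improvement. The protocol fixes one covariate set for three separately analysed populations, does not name baseline items it already records, and does not define clinical status or its time point. The benefit of naming them is some precision on duration, protection against chance imbalance in presentation, and a reproducible adjusted model.

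For the neonatal groups the gain is about 1.5, 2.9 or 5.6 percentage points of power at an assumed R² of 0.05, 0.10 or 0.20. For children it is essentially a narrower interval. These sizes rest on the plan's 1.4 days and SD 5, removal of the full 20%, and an R² that the documents do not supply. The common set is not a validity error.

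**What to change.** In the Data analysis section, keep sex, age and clinical status. Define clinical status and state that it is the value at enrolment, before randomisation. Then add to the adjusted duration model:
- **Children:** entry criterion (fever, diarrhoea or both) and symptom duration.
- **Neonates with suspected sepsis:** symptom duration.
- **At-risk newborns:** the WHO risk factor or factors present.

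Add a birth variable, such as gestational age or birth weight, only once the background form is confirmed to record it, because the protocol names neither. Fix the lists before outcome data are seen.

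The cost is wording and a few model terms: about three for children, one for neonates with suspected sepsis, and one per risk factor for at-risk newborns, against roughly 517 evaluable participants (2 × 258.4) in each neonatal group. No extra patients are needed. One practical check: Study procedures places randomisation between screening and the first-consultation form, so confirm that clinical status and symptom duration are captured before allocation is known.
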